## Abstract

Supplemental Digital Content is available in the text

## Introduction

1

Kidney transplantation (KT) is a surgical replacement procedure to remove a healthy, functioning kidney from a living or deceased donor and implant it into a patient with end-stage renal disease. The short and long-term outcomes after KT are largely determined by the patient's adherence to a complex and ongoing set of medical recommendations, aimed at minimizing the risk of graft loss and comorbid complications.^[1,2]^ Self-management is intended to help patients to maintain wellness in their foreground perspective. Self-management programs must include content that addresses the following 3 tasks: medical or behavioral management, role management, and emotional management.^[3]^ For KT recipients, self-management tasks include adhering to an immunosuppressive regimen, monitoring for signs of major complications (ie, rejection, infection, and malignancies), keeping regular appointments with the nephrologists, and diet management.^[1,3,4]^

Previous studies have shown that non-adherence to immunosuppressant is associated with 60% increased risk of graft rejection among KT recipients.^[5]^ Moreover, a recent longitudinal study has proved that the patients with appointment non-adherence had 1.5 times higher risk of acute rejection and 65% higher risk of graft loss.^[6]^ Several observational studies have published high non-adherence rates to lifestyle recommendations.^[7,8]^ Kobus et al have shown that 85.3% of patients did not change their diet after KT and 64.2% were not aware of dietary recommendations.^[8]^ Adherence to recommended lifestyle is critical to maintain the positive prognosis as well as health-related quality of life (HRQoL). Employing self-management programs might be useful to help patients adapt a proper lifestyle.^[9]^

In developing countries, widespread use of mobile devices and almost universal coverage of signal network has given mobile-based interventions (m-Health) a higher opportunity to be more affordable, effective, and accessible among patients.^[10–12]^ It has been previously proved that m-Health interventions have become successful to obtain objectives in low-income countries in an economically viable and sustainable way.^[13,14]^ The m-Health interventions can be used to provide educational and supportive contents, reminders, and immediate response to patients’ questions aiming to overcome weak access to information and limited human resources.^[15–17]^

The integration of telephony with computers has created an advancement in health information technology called interactive voice response system (IVRS), which, in particular, has emerged in the form of many applications dealing with chronic disease management.^[16,18,19]^ Using IVRS, patients interact with a set of organized voice-recorded message components and are able to respond to queries using their touch-tone phones. The IVRS offers a way to help individuals address their health literacy issues. Since the per-contact cost of IVRS is low, frequent health monitoring messages can be sent to ensure continuous contact with patients.^[20]^ In addition, since patients carry their mobile phone with them wherever they go, the occurrence of missing or unsuccessful calls are very unlikely.^[18]^

Many IVRS applications in healthcare have recently been explored. For instance, a recent review on the effectiveness of IVRSs for managing chronic conditions concluded that these interventions are useful to change patients’ behaviors and, consequently, improve health-related outcomes.^[21]^ Furthermore, other studies have shown that patient education is the best way to effectively improve medication adherence. Depending on the type of non-adherence and the patient's profile, the use of a combination of educational interventions (eg, patient education, self-care, and patient motivation) has the greatest potential to improve medication adherence.^[22–25]^

Health education programs are aimed to improve outcomes, increase the benefits for the community, and, consequently, enhance public health.^[26]^ More specifically, the program logic model (PLM) helps to identify the measurable outcomes in the causal chain.^[27]^ PLM offers a framework to guide the content of e-health education programs, enabling the healthcare providers to more effectively define and measure objectives, empower patients, and improve patient care.^[28]^ The PLM will be used during the development and implementation phases of this study. According to the PLM, patient education results in proximal outcomes (eg, knowledge and compliance) and intermediate outcomes (eg, self-efficacy and QoL). As a long-term effect, patient education programs might decrease or eliminate the loss of productivity, increase community capacity, and increase the efficiency of health care resources. Since post-transplant management is a complex process and KT recipients have a lot to learn, inadequate patient knowledge can easily result in dire consequences (eg, decreased adherence to recommendations and organ rejection).^[29,30]^ We hypothesized that automatic IVRSs designed based on educational and theory-driven intervention which is acceptable to the individual patient would improve self-management in KT recipients who received IVRS compared to patients who only received usual care. Thus, we designed a randomized, 2 parallel groups controlled trial to evaluate the effect of an IVRS intervention on self-management outcomes (such as immunosuppressant medication adherence, transplant knowledge, and quality of life) among KT recipients.

## Theoretical framework

2

Behavior and behavior change are described as the critical components of a self-management process for chronic diseases.^[33]^ According to Barlow and colleagues, self-management is defined as the ability of the patient to manage the symptoms of complications, treatment approach, physical and psychosocial issues, and lifestyle patterns.^[34]^

The intervention in this study was based on the self-regulation theory,^[35]^ which describes how patients understand their illness and how they establish coping strategies to manage their condition.^[36]^ In this theory, while a patient is considered as an “active problem-solver,” the role of both cognitive and emotional processes determines the illness perceptions and associated coping strategies (ie, self-management behaviors).^[36]^ Moreover, the self-regulation theory suggests that relevant factors should be displayed by the content of interventions including accurate information, creating behavioral skills and supplying effective support.^[37]^ This theory focuses on the patient's personal model to determine his/her behavioral responses to illness. Five core elements are identified for transplant representations: identity, cause, timeline, consequences, and treatment effectiveness.^[38]^ Some environmental modifications can be used to enhance the self-regulation process, such as the reminder systems. These systems promote the patient's self-efficacy by eliminating the barrier of forgetfulness.^[39]^ Cost-effectiveness of such systems helps researchers to manage patient adherence.^[40,41]^

## Methods

3

### Design and development of IVRS

3.1

We used the following phases to design and develop our IVRS:

#### Preliminary study to investigate patient requirements

3.1.1

In a preliminary study, non-adherent immunosuppressive patients were determined by basel assessment of adherence to immunosuppressive medications scale (BAASIS).^[31]^ Also, in this group of patients, barriers to medication non-adherence were determined by the immunosuppressive therapy barriers scale.^[32]^ Our investigation in patient requirement identified the barriers to adherence as follows: use of multiple pills of immunosuppressive medications at 1 time, lack of understanding about the usefulness of immunosuppressive medications, confusion about medication taking, and difficulty in remembering the medication taking.

#### Educational content

3.1.2

An expert group was created, consisting of a group of nephrology specialists, patient education specialists, nurses, and medical informatics specialists. Three focus group sessions with 10 individuals were formed to determine provider expectations of these patients over a period of 8 hours. In this focus group, the booklet related to transplant patients was reviewed and educational content was corrected and confirmed according to the patient requirements and provider expectations. Educational content consisted of the following 7 sections:

(1)Immune system and its role in rejection.(2)Immunosuppressive medications and complications.(3)Infections and methods for prevention.(4)Nutrition.(5)Long term care.(6)Return to work and life.(7)Sexual activities and pregnancy.

Each section consisted of between 2 and 8 subsections.

An additional file shows more details about the export group, (see Supplemental file 1).

#### Patient profile

3.1.3

A Delphi round by the expert group determines the data elements needed for the patient profile. The final profile of the patient consists of 5 main categories, including:

(1)Demographic information (unique number, age, gender, educational level, mobile phone number, city, type of residence, and patient address)(2)Medical information (date of transplant, donor)(3)Type of immunosuppressive medication and usage intervals,(4)Patient's passcode(5)Date of referral and patient's follow up.

We need the information in the profile to make individualized IVRS's calls and reminders.

#### IVRS development

3.1.4

The IVRS consisted of several technologies working together in order to schedule, receive, enter, and record automated phone calls. We used the Linux Cent operating system, VoIP network, PHP as the Programming language to write IVR call flow/script and MySQL server as a database that connected to the Asterisk server. IVRS is implemented by installing the Asterisk server on the host machine and creating virtual machines. One e1 line is connected to the VoIP network to transfers out the phone calls. For each patient, all patient profile information and setting calls must be entered. Also, every interaction of the system with the patient will be recorded in the patient profile as patient's reports. Patient reports also contain the date, time and content of short messages service (SMSs) and phone calls.

Figure 1 shows a screenshot of the web application for managing our proposed IVRS. The boxes at the top of the figure show some important statistics such as the number of calls and SMSs. The diagram reveals calls’ status in the previous 30 days, where blue bars show the number of all calls in that day, green nodes indicate the number of completed calls, and red nodes represent the number of missed calls. The main menu at the left of the figure navigates the administrator of the IVRS to other pages of the application. It is worth noting that the only user of this application is the administrator of the IVRS. An additional file shows more details about the application, (see Supplemental file 2).

**Figure 1 F1:**
[figure not shown]
A screenshot of the web application for managing the IVRS. IVRS = interactive voice response system.

#### Pilot implementation of IVRS

3.1.5

Information on 10 KT recipients (who were not considered for final evaluation) was entered into IVRS with preset reminders and educational calls. After 2 weeks, the same 10 participants were called and asked some questions about their experience with the working with the system, particularly focusing on their satisfaction, ease of use and possible problems with the system. Ninety percent of KT recipients expressed that they were satisfied and interested in the sent reminders and educational calls. An additional file shows more details about the questions, (see Supplemental file 3).

### Evaluation IVRS

3.2

#### Study design

3.2.1

A randomized, 2 parallel groups, controlled trial in accordance with the Consolidated Standards of Reporting Trials guidelines^[33]^ was designed (Fig. 2). The protocol is reported in accordance with the Standard Protocol Items: Recommendations for Interventional Trials 2013 Statement.^[34]^

**Figure 2 F2:**
[figure not shown]
Consort diagram.

#### Study setting

3.2.2

The study will be conducted in Montaserieh Transplant Center in Mashhad, Khorasan Razavi province, northeastern Iran. Montaserieh is the only specialized governmental referral educational hospital providing organ transplantation in northeastern Iran. The center is affiliated with Mashhad University of Medical Sciences (MUMS).

### Participants

3.3

KT recipients who will be referred to the center in July 2018 for follow up visits and caretaking are screened for eligibility. Eligible patients will be asked to provide consent with appropriate trail information and enough time to study and ask questions. Patients will be received 2 types of information related to the study:

(1)fully understandable oral information(2)2informed consent, in which the study design is described completely.

Informed consent has already been evaluated by the Ethics Committee of MUMS (IR.MUMS.fm.REC.1396.160). We ensure participants can withdraw from the study at any time without any commitment and no effect on their subsequent care. Eligible participants will be included after completing informed consent.

The inclusion criteria are as follows:

(1)KT recipients who have received a KT between 20 March 2012 and 20 March 2017,(2)having 18 years of age or more,(3)having acceptable graft function (do not need any types of dialysis),(4)having access to a mobile phone,(5)being able to read the informed consent information, and(6)willingness to participate.

The patients who are refused to participate in the study will be excluded. KT patients will be randomly assigned to the control (usual care) or intervention (usual care plus IVRS) groups. Usual care includes an educational booklet for KT and patient education provided by the nephrologists.

### Interventions

3.4

Three types of completely automatic calls will be received by KT patients through the IVRS.

#### Reminder call

3.4.1

The purpose of a reminder call is to remind the patient about the time for taking immunosuppressive medications and periodic appointment. Medication reminder calls will be done once a day based on the type of immunosuppressive medications which are recorded in the patient profile. The IVRS will contact the patient's mobile number and remind them about taking their medication. In the absence of an answer, the system will call again 30 seconds later, and if she\he does not respond, it will send a text message containing the medication reminder.

The periodic appointment reminder calls will be done every 2 months based on the date of referral which is recorded in the patient's profile a day before their appointment. Moreover, on the day of appointment, patients will receive a reminder in the form of an SMS.

#### Educational calls

3.4.2

Educational calls, which contain information about self-management education in KT patients, are made every day based on educational content to improve patient transplant knowledge. These messages are recorded with a clear voice. This part of IVRS is patient-centered, whereby calls are made at specific times determined by the patient. Entering contacts menu will be created so that KT patients can dial [name] and after record passcode, they can access to classified educational information.

#### Medication adherence call

3.4.3

Medications adherence calls measure immunosuppressive adherence on a daily basis. These calls are designed to encourage the patient to answer 2 questions at the end of the day. The first question is concerned with taking the immunosuppressive medication and the second one is about delayed timing. The participant is asked to answer the questions using the phone keypad. Answers include 0 = never, 1 = once, 2 = twice, 3 = more than twice. Patients selecting an answer other than “never’” were considered as non-adherent in that day. Every 10 days, the system sends a feedback based on patient's answers. Feedbacks will be provided in the form of an SMS. The content of this message will reveal the status of patient adherence (very poor, poor, moderate, good, and excellent) and will contain a motivating message.

Participants can withdraw from the study at any time and for any reason. The researchers can remove a participant from the study if they miss more than 2 follow-up visits or if they need some type of dialysis based on a nephrologist's expert opinion.

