### Outcomes measure

3.5

Study outcomes will be evaluated in accordance with Table 1. Primary and secondary outcomes are measured at baseline, and at 2-months, 4-months, and 6-months after baseline. For ethical reasons, if the intervention is found to be effective, all groups will have access to IVRS at the end of the intervention. Primary outcome will be immunosuppressive medication adherence that is evaluated based on a self-report in both groups during the follow-up period. The secondary outcomes include transplant knowledge, HRQoL, and rehospitalization rate.

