Rehospitalization was defined as any unscheduled rehospitalization (our program does not hospitalize for routine follow-up evaluation). The total number of rehospitalization days over the duration of the study, as measured by the cumulative number of hospitalization days over this time period, were extracted from the hospital information system and participants’ medical records.

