## Discussion

5

IVRS has been used in different parts of health care including after hospital discharge to encourage test adherence, medication adherence in patients with asthma and human immunodeficiency virus, heart disease and self-management in back pain and post-stroke.^[37–43]^ IVRSs are used in medication adherence in different conditions with different functions.^[5,41,44–47]^ Previous studies showed that providing information about the health consequences appeared effective in promoting medication adherence. Such information usually includes the advantages of taking medications or the disadvantages of not taking them.^[42,48]^ In this study, we tried to design an intervention based on barriers for immunosuppressant medication adherence. We will evaluate the effect of educational, reminder, and feedback interventions not only in immediate outcomes such as knowledge and medication adherence, but also on intermediate outcomes such as quality of life and follow-up visits.

An important aspect of our study is that it is based on a behavior change theory. Theory-based interventions can make effective changes in behavior.^[6–8]^ The incentives might be used to reduce intentional and unintentional barriers. We hypothesized that feedback with an incentive message might be more effective than other forms of incentives. Thus the RCT will be conducted in KT recipients to evaluate the effects of the IVRS on improvement of patient self-management. In particular, m-health interventions provide tangible incentives in the form of feedback, which have the potential to warn patients about their health conditions. The interactive elements in the IVRS can potentially help providers to realize the patient self-management or measurement of patient-reported outcomes and examine the process of behavioral changes.

One of the limitations of present is that behavioral change observed during any controlled study may not be directly translated into clinical practice. Change in adherence behavior reached over the period of the study may not be maintained after the program ends. Moreover, an automated program may not effectively satisfy the requirements and needs of all groups of patients.

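### Section 3.4.3 lets researchers remove randomised patients from the study after missed visits or dialysis, which can lose obtainable follow-up data selectively and unequally by arm

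*Protocol article*

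**What the plan says.** The rule stands at the end of section 3.4.3 of the protocol article: researchers can "remove a participant from the study if they miss more than 2 follow-up visits or if they need some type of dialysis", the latter in a nephrologist's judgement. The wording is permissive, and it concerns leaving the study, not merely stopping the calls. Nothing in the article says that a removed patient stays in follow-up.

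Other sections bear on it:

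- Section 3.4.1, on the intervention: "The periodic appointment reminder calls will be done every 2 months", with a text message on the day itself. Usual care (section 3.3) is a booklet and education by the nephrologists.
- The Discussion names "intermediate outcomes such as quality of life and follow-up visits" among the things the intervention is expected to change.
- Section 3.3 requires patients to be free of dialysis at entry.
- Section 3.5 places the post-baseline assessments "at 2-months, 4-months, and 6-months after baseline".
- Section 3.10 says that rehospitalisation days are "extracted from the hospital information system and participants’ medical records".
- Section 3.9 blinds physicians and outcome evaluators, but excepts the clinical trial team and the research assistant.

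**The concern.** Randomisation makes the arms comparable only while the patients who were randomised are followed. Here patients may leave because of something that happened after allocation, and one of the two triggers is something the intervention acts on directly. If reminders improve attendance, more control than IVRS patients could meet the missed-visit criterion. If daily calls tire patients, the reverse could happen.

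The removed patients are also unlikely to be typical. The Introduction reports that "non-adherence to immunosuppressant is associated with 60% increased risk of graft rejection among KT recipients", and cites a 65% higher risk of graft loss with missed appointments. On the article's own reasoning, patients who stop attending or lose graft function tend to be those who are doing badly. Discretion adds to the problem, because the decision may rest with people who know the allocation.

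At stake are the completeness of a secondary outcome that needs no visit, and the later assessments of patients who start dialysis.

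**Working it through.** **Figures in the plan.** The article states no removal, attendance, dialysis or adherence rate. Its only attrition figure is the 50% allowance in section 3.6, where 40 × (1 + 0.5) = 60 per group. That covers overall loss and says nothing about removal by researchers.

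**Step 1: timing.** Patients enter without dialysis (section 3.3), and follow-up visits come after baseline. Both triggers are therefore post-randomisation events.

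**Step 2: link to allocation.** For attendance the link is direct: the reminders go to one arm only (section 3.4.1). For dialysis it is indirect. Dialysis and graft loss are not outcomes in section 3.5, and the path runs from non-adherence through rejection and graft loss, as described in the Introduction.

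**Step 3: reach of the missed-visit trigger.** Section 3.5 has 3 post-baseline assessments, and reminders every 2 months over 6 months also give 6 / 2 = 3. More than 2 of 3 means all 3. On this reading the trigger applies only to patients who attend nothing, and is met only at month 6. If BAASIS, K-TUT and SF-12 are completed at visits, these patients have no post-baseline values with or without the rule. What the rule adds is the possible loss of their rehospitalisation data. The article does not define the visits that count. If other clinic visits count, the trigger reaches patients who still attend some assessments, and the loss is wider.

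**Step 4: reach of the dialysis trigger.** This can act at any time. A patient removed at month 3 loses the 4- and 6-month assessments and possibly the rest of the hospital record. The repeated-measures ANOVA, Friedman and Cochran tests in section 3.12 need complete data in their standard form, so the month-2 values could be lost too.

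**Step 5: how removal shifts a comparison (illustration only).** Let p be true adherence in an arm, p_r adherence among those removed, and r the share removed. Then

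observed = (p − r·p_r) / (1 − r), so observed − true = r(p − p_r) / (1 − r).

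Assume no true difference between the arms. All values of p, p_r and r below are assumptions.

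With p = 50% and p_r = 15%:
- Removal 20% control, 5% IVRS: 0.470 / 0.80 = 58.75% against 0.4925 / 0.95 = 51.8%, an apparent −6.9 points for IVRS.
- Removal 30% control, 10% IVRS: 0.455 / 0.70 = 65.0% against 0.485 / 0.90 = 53.9%, an apparent −11.1 points.

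With p from 40% to 60%, all removed patients non-adherent (p_r = 0, observed = p / (1 − r)), 60 randomised per arm and a two-sided 5% two-proportion z-test:

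| Removed, control v IVRS | IVRS minus control (points) | Rejection rate with no true effect |
|---|---|---|
| 10% v 10% | 0 | 5% |
| 10% v 5% | −2.3 to −3.5 | 5.7% to 6.7% |
| 15% v 5% | −5.0 to −7.4 | 8.1% to 12.8% |
| 20% v 5% | −7.9 to −11.8 | 12.7% to 25.2% |

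Of 60 patients, 5% is 3 and 20% is 12. Exchanging the arms reverses the sign and favours IVRS. The same identity holds for mean hospital days: if removed patients have more days than average, that arm's mean is understated.

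By Step 3, these adherence figures do not measure the missed-visit trigger on the three-assessment reading. The adherence of patients who attend nothing is missing whether or not they are formally removed.

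**The case against.** The strongest reply has four parts.

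1. **The rule is permissive.** It does not say that data already collected, or hospital records, are dropped, and section 3.12 excludes nobody. Analysis sets and missing data are commonly settled in an analysis plan, which is not shown. This stands to the extent that an undefined analysis set is no finding and deletion of data is not established. It does not answer the point about conduct: assessments never made because a patient has left the study cannot be restored by a later definition.
2. **The missed-visit trigger adds little to ordinary attrition** if it means all three assessments. This stands for adherence, knowledge and quality of life. It does not cover rehospitalisation, which needs no attendance.
3. **Dialysis may be uncommon within six months.** Patients were transplanted by March 2017 and screened in July 2018, at least 15 months later, with acceptable graft function. The need is judged by a nephrologist, and section 3.9 has physicians blinded. This limits the likely number, although the article gives none, and the decision to remove still lies with the researchers.
4. **The assumed removal shares have no source.** This stands. Shares of 20% to 30% would need that many patients to attend nothing or start dialysis.

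**Conclusion.** The point holds as a matter of trial conduct. The rule allows discretionary removal of randomised patients, by a team that is not blinded, for events after allocation. One of those events is directly affected by the intervention. The resulting loss can be selective and unequal, and much of it is avoidable.

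On the three-assessment reading, the avoidable part is mainly record-based rehospitalisation, plus later adherence, knowledge and quality-of-life data from patients who start dialysis. It is larger if other clinic visits count. Both statements assume that removal from the study ends data collection, which the wording implies but does not spell out.

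The size and direction of any bias cannot be determined from the document. A reader might infer that the primary adherence comparison is off by some 7 or 11 points, or that adherence is overstated in both arms. The documents support neither: the inputs are assumed, and for patients who attend nothing the figures describe attrition that would occur without the rule. Nor do they show that the intervention is designed to prevent dialysis, or that removed patients' existing data will be deleted. The point merits a change of wording. It is not a ground for calling the primary result biased.

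**What to change.** - Reword the rule in section 3.4.3 so that missed visits and dialysis do not end study follow-up. Any clinical decision about stopping calls or managing dialysis stays with the investigators. The article has no separate rule for stopping calls, and this comment proposes none.
- State that every randomised patient stays in follow-up and is analysed in the allocated group.
- Extract rehospitalisation from the hospital system and records to month 6 for everyone, except those who withdraw consent for use of their data.
- When a visit is missed, attempt the four-item BAASIS by telephone under the same rule in both arms, and record the mode of collection.

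I would not count patients who start dialysis as non-adherent, even in a sensitivity analysis. BAASIS measures missed, mistimed or reduced doses, and graft failure is a different thing.

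The cost is protocol wording, a few telephone contacts, and some BAASIS data collected by a second mode, possibly more in one arm if attendance differs. Recording the mode lets that be examined. The article reports recruitment as incomplete, so the change could still be made.
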